**Figure 1 Fig1:**
[figure not shown]
**Flowchart of the study.**

If pulpal exposure occurs during excavation, a pulpotomy will be attempted. This will be provided according to dental routine, using ferric-sulfate for hemostasis and a calcium hydroxide dressing. Teeth with amputated pulps will be restored via stainless steel crowns if necessary. If no amputation is possible, teeth will be extracted. All retained teeth will be followed up on regardless of the treatment arm.

Data collection will be performed via case reports forms. The following data will be collected after the initial or second-step treatment:Anesthetic and restorative material used,Patients’ cooperation (1 to 4) [24],Subjective assessment of patient (visual analogue scale),Subjective assessment of parent (grade 1 to 6),Subjective assessment of dentist (grade 1 to 6),Transportation time and costs, andTime, staff and material required for treatment.

During follow-up examinations, the following parameters will be assessed:Tooth retreated at another clinic (yes or no),Tooth exfoliated (yes or no),Sensitivity and symptoms, andRestoration integrity [22].

If retreatments are required, the cost of these will be assessed as well. Retained, retreated teeth will be followed up on to assess the survival of these teeth regardless of retreatment. A summary of performed procedures and recorded data can be found in Table 2.

**Table 2 Tab2:** **Timing of measurements**

**Measures**	**Preoperative**	**First step**	**After six month/second step**	**Follow-up**	**Retreatment**
Demographics	x				
Dental history	x				
Caries risk	x				
ICDAS score	x				
Sensitivity testing	x	x	x	x	
Radiographic depth	x				
Radiographic endodontic status		(x)	(x)	(x)	(x)
Dental anxiety	x				
Cooperation		x	x		x
Subjective assessments		x	x		x
Costs (time, staff and material)		x	x		x
Clinical outcomes			x	x	x

### Data analysis and statistical evaluation

The statistical evaluation will be performed using SPSS 20.0. Descriptive statistics will be calculated according to distribution of data. Log rank tests will be used to compare success and survival between groups, with effects of possible confounders (age, gender, dental anxiety, cooperation, use of local anesthetics, caries risk, dental arch, first or second molar, surfaces and center) being assessed. Moreover, we will use two-sided independent t tests or Mann-Whitney U test (to compare visual analogue scale results and costs) as well as chi-square tests (to compare restorative integrity and subjective grading of treatments).

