**Methods/Design:**

The planned study is a prospective multicenter, two-arm parallel group, randomized controlled clinical trial comparing selective and stepwise excavation in deciduous molars with deep, active caries lesions without pulpal symptoms. We will recruit 300 children aged between three and nine-years-old with a minimum of one such molar. Patients participating in another study, or those with systemic diseases, disabilities or known allergies to used materials as well patients with teeth expected to exfoliate within the next 18 months will be excluded. After inclusion, sequence generation will be performed. Initial treatment will follow dental routine. During excavation, leathery, moist and reasonably soft dentin will be left in proximity to the pulp followed by adhesive restoration of the cavity. Afterwards, patients’, dentists’ and parents’ subjective assessment of the treatment will be recorded using visual analogue or Likert scales. Re-examination will be performed after six months, and only then teeth will be allocated to one of the two interventions. Selectively excavated teeth will not be treated further, whilst for stepwise caries removal, a second excavation will be performed until only hard dentin remains. Clinical re-evaluations will be performed after 12, 24 and 36 months. Restorations will be reassessed using modified Ryge criteria. Objectively or subjectively required retreatments will determine success and survival. Retreatments will be evaluated both subjectively and regarding generated costs.

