### Sample size

The required sample size was calculated based on the primary outcome parameter, success (see below). We anticipate a hazard ratio of 1.3 [21] of stepwise excavated compared with selectively excavated teeth. If α = 0.05 and 1-β = 0.9, a sample size of n = 66 per group is required. Assuming an annual drop-out rate of 20%, 114 patients per group will be required. The total required sample size would thus be n = 228. To allow possible subgroup analyses, a total of 300 patients will be recruited (n = 100 per center).

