### Allocation and blinding

If more than one primary molar is eligible, the decision as to which tooth will be included into the study will be performed using random number tables (WH) before treatment is commenced. Sequence generation will be performed after inclusion via random number tables (WH). Allocation will be performed via sealed opaque envelopes after the six-monthly recall examination (six months after selective excavation) by the treating dentists. Thus, both the first excavation step and the first re-examination will be performed blinded as to whether further excavation will be performed or not. Clinical follow-up examinations will also be performed blinded to treatment group allocation. Blinding during the second excavation step and blinding of patients as to which treatment was performed will not be possible, but patients will be informed not to reveal treatment allocation to the examiner during follow-up examinations.

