### Outcomes

Outcomes will be assessed by the treating dentists or study nurses. The primary outcome of the study will be success (not requiring any re-intervention). Secondary outcomes will include survival (not requiring extraction), restoration integrity, assessed via modified USPHS-criteria [13], patients’ subjective assessment of the treatment using a visual analogue scale (for stepwise excavation, assessments will be performed twice and mean visual analogue scale results will be calculated), dentists’ and parents’ subjective assessment of the treatment using grades 1 (very good) to 6 (very bad) and initial and follow-up treatment costs (calculated by combining costs for staff, as assessed by time required for the procedures and the number of personnel involved, and costs for transportation of patients or materials).

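### The only method named for the primary outcome is a log-rank test, with no effect estimate and no model for the ten listed covariates; a prespecified centre-stratified Cox model on pre-allocation data would be a cheap improvement

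*Protocol article*

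**What the plan says.** All references are to the protocol article.

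- **Data analysis and statistical evaluation:** "Log rank tests will be used to compare success and survival between groups, with effects of possible confounders" being assessed. The variables are "age, gender, dental anxiety, cooperation, use of local anesthetics, caries risk, dental arch, first or second molar, surfaces and center". No regression model, effect measure, confidence interval, coding or time of measurement is given for them. The same section names a specific test for each of the other comparisons it covers.
- **Sample size:** "We anticipate a hazard ratio of 1.3 [21] of stepwise excavated compared with selectively excavated teeth".
- **Allocation and blinding:** "Allocation will be performed via sealed opaque envelopes after the six-monthly recall examination".
- **Intervention and data collection (text after Figure 1):** "The following data will be collected after the initial or second-step treatment", and the list that follows includes the anesthetic used and the child's cooperation. Table 2 marks cooperation at the first step, at the six-month or second-step visit, and at retreatment.
- **Abstract, Methods/Design:** "Selectively excavated teeth will not be treated further". A second treatment therefore takes place in the stepwise arm only.

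**The concern.** Three things do not fit together.

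1. The planning parameter is a hazard ratio, but the one named method returns a p-value. Read literally, the trial would report whether the arms differ in success, but not by how much or how precisely.
2. A log-rank test can be stratified on a factor or two. It cannot carry ten covariates, one of which (age) is continuous. Applied to one covariate at a time, it leaves the comparison of arms unadjusted for centre and for prognostic baseline data.
3. Cooperation and anesthetic use have no fixed measurement time. First-step values precede allocation and are safe to adjust for. Second-step values follow from the allocated treatment, and retreatment values from the failure event.

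At stake are an effect estimate for the primary outcome, some precision, and protection against an adjusted analysis that conditions on a consequence of treatment.

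**Working it through.** **Plan's own figure.** The article gives 66 per group for a hazard ratio of 1.3, α = 0.05 and power 0.90. The two-sided Schoenfeld formula gives events = 4(1.960 + 1.282)²/(ln 1.3)² = 42.03/0.0688 ≈ 611. The 66 is not reproduced: with an event in all 132 teeth, power would be about 33%. That is a separate and larger problem. It matters here only because adjustment cannot repair it.

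**Can a log-rank test carry the ten factors?** With two levels for each of nine factors and three centres, there are at least 2⁹ × 3 = 1,536 strata for 300 children.

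**Simulation A (the kind of model proposed).** 300 children, 36 months, 20% yearly loss, 1,000 runs. Assumed covariate effects: hazard ratio 2.5 for a binary factor, 1.5 per SD of age, and centre log-hazards of −0.4, 0 and +0.4. Power:

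| True HR | 36-month failure, reference | Unadjusted log-rank | Centre-stratified Cox, 2 covariates |
|---|---|---|---|
| 1.3 | 20% | 16% | 17% |
| 1.3 | 35% | 21% | 24% |
| 2.0 | 20% | 77% | 81% |
| 2.0 | 35% | 90% | 95% |

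**Simulation B (varying prognostic strength).** 228 children, 3 years, 20% yearly loss, 30% three-year baseline failure, 400 runs. The covariates give the log hazard an assumed SD of 0, 0.5 or 1.0. Power:

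| True HR | SD | Unadjusted log-rank | Log-rank stratified on all ten | Cox, ten covariates | Cox minus unadjusted |
|---|---|---|---|---|---|
| 1.3 | 0 | 17.0% | 3.25% | 18.0% | +1.0 |
| 1.3 | 0.5 | 16.25% | 3.25% | 16.5% | +0.25 |
| 1.3 | 1.0 | 14.5% | 2.75% | 23.0% | +8.5 |
| 2.0 | 0 | 83.25% | 7.0% | 80.75% | −2.5 |
| 2.0 | 0.5 | 76.25% | 9.0% | 80.0% | +3.75 |
| 2.0 | 1.0 | 63.25% | 8.5% | 81.5% | +18.25 |

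At a hazard ratio of 1.0 the unadjusted test rejected in 3.5%, 5.75% and 6.25% of runs, consistent with 5%. The Monte Carlo standard error of one power figure near 80% is √(0.8 × 0.2/400) = 2 points, so differences of a few points are not firm. Neither simulation models the six-month delay before allocation.

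**How many covariates?** Assume 20% fail by 36 months and all losses are censored. Then λ = −ln(0.8)/3 = 0.0744 and μ = −ln(0.8) = 0.2231 per year. The expected event share is λ/(λ+μ) × [1 − exp(−3(λ+μ))] = 0.25 × 0.590 = 0.148, or about 44 of 300. Ten covariates need at least 9 + 2 = 11 parameters (two for three centres), so about 44/11 = 4 events each if all entered one model. This supports a short list.

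**Adjusting for a value taken after allocation.** In the simulation an unmeasured trait drives both cooperation and failure, and treatment shifts later cooperation by an assumed log-odds of 0, 1 or 2:

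| True HR | Shift | Adjusted for first-step value | Adjusted for later value |
|---|---|---|---|
| 1.0 | 0 / 1 / 2 | 1.00 / 0.99 / 1.00 | 1.00 / 0.91 / 0.85 |
| 1.3 | 0 / 1 / 2 | 1.29 / 1.28 / 1.30 | 1.29 / 1.18 / 1.11 |

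First-step values leave the estimate essentially where it was. Later values pull it down as the shift grows.

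**The case against.** The strongest reply is that nothing here is an error. The log-rank test is valid in a randomised trial, and its standard sample size formulas take a hazard ratio as input. A hazard ratio with confidence interval can be reported beside it. An article condenses a longer protocol, and the model for the covariates may stand there or in an analysis plan. This stands as far as it goes. The point is therefore not that detail is missing, but that the one method stated for the primary outcome can be bettered with data the trial already collects.

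Some stronger readings are tempting and should not be drawn:

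- *The primary comparison is unadjusted.* This is an inference. The text says covariate effects are assessed, without saying how.
- *Power is lost and bias enters.* These are alternatives. Power is forgone only if the comparison is unadjusted. Post-allocation bias arises only if it is adjusted for the later values. Nothing in the article says those values will be used, and since the second treatment exists in one arm only, it would take something like a latest-value rule to bring them in.
- *Covariates will be chosen from the data.* The article gives a fixed list and mentions no selection step.
- *The model is bound to be overloaded.* The article does not say that all ten enter one model, and it gives no failure rate. The 44 events also assume censoring of losses, as in Table 3. The Missing data section counts drop-outs as non-success, which would give more events.

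The gain at the planned hazard ratio is also modest: 1 to 3 points in Simulation A, and about 0 to 9 in B.

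**Conclusion.** The point holds as a cheap improvement, not as a flaw that invalidates the primary test. The article plans on a hazard ratio, names a test that does not estimate one, and lists ten covariates without a method that could hold them together.

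The gain in power is conditional on prognostic strength, which the article does not give. At an assumed hazard ratio of 2.0 it runs from about nil to about 18 points. At 1.3 it is small in absolute terms, and power stays below 25% with either analysis. The effect estimate and its interval are gained whatever the prognostic strength.

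The timing of cooperation and anesthetic use is a caution: the article fixes neither value, and only the later ones would do harm. The sizes shown for that bias (1.3 moving to 1.18 or 1.11) rest wholly on the assumed shifts.

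**What to change.** In the analysis section, state that:

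- the primary analysis of success is a Cox model stratified by centre, with allocated arm and two or three prespecified covariates measured before allocation (for example age and number of surfaces);
- the result is the hazard ratio with its 95% confidence interval;
- a log-rank test stratified by centre is reported as support;
- any adjusted analysis takes cooperation and anesthetic use at the first step only, never at the second step or at retreatment.

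The cost is a change of wording, with no new data. There is a small downside: the covariates must be fixed in advance, and the hazard ratio is then conditional on them.

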### Objectives and hypotheses

The study aims at comparing the success (the probability of not requiring any re-interventions) and the survival (the probability of not requiring tooth removal) of selectively excavated versus stepwise excavated vital, non-symptomatic deciduous molars with deep lesions. In addition, we assess the restoration integrity of selectively excavated versus stepwise excavated deciduous molars, evaluate the preference of patients, parents and dentists for one of both strategies, and comparatively assess the costs associated with each strategy.

Our primary hypothesis is that success rates differ significantly between selectively excavated and stepwise excavated teeth. Secondary hypotheses are that restoration integrity is assumed to significantly differ between selectively excavated and stepwise excavated teeth. Moreover, we hypothesize that patients’, parents’ and dentists’ preference is significantly different for selectively excavated versus stepwise excavated teeth. Eventually, both initial and long-term costs of excavation methods are supposed to significantly differ.

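### The child VAS comparison sets one rating (selective) against a mean of two (stepwise) and permits Mann-Whitney, which can falsely show a preference difference when ratings are skewed

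*Protocol article*

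**What the plan says.** Four statements in the protocol article together fix the comparison.

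- **Score, stepwise arm** (Outcomes): "for stepwise excavation, assessments will be performed twice and mean visual analogue scale results will be calculated".
- **Score, selective arm**: the article does not state this separately. The abstract says "Selectively excavated teeth will not be treated further", and the list of collected data under Intervention and data collection opens with "The following data will be collected after the initial or second-step treatment". Averaging is specified for stepwise only. A selective child therefore contributes one rating. This is an inference: Table 2 marks subjective assessments in the six-month/second-step column without naming an arm.
- **Test** (Data analysis and statistical evaluation): "two-sided independent t tests or Mann-Whitney U test (to compare visual analogue scale results and costs"). The article gives no rule for choosing between the two.
- **Interpretation** (Objectives and hypotheses): a secondary hypothesis is that "patients’, parents’ and dentists’ preference is significantly different for selectively excavated versus stepwise excavated teeth".

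Nothing in the article adjusts for the unequal number of ratings.

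**The concern.** Mann-Whitney tests whether two groups come from the same distribution; in practice it responds to P(stepwise > selective) departing from one half. The mean of two ratings has the same expectation as one rating from the same marginal distribution. Unless the two ratings are perfectly correlated, though, it has a different shape. With a skewed scale, or many children marking one end, averaging pulls scores away from that end. The rank test can then pick up the number of ratings rather than any difference between the strategies.

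Skew is also the usual reason for preferring Mann-Whitney to a t test, so the affected option is most likely to be used where it misbehaves. At stake is whether a significant child VAS result can be read as a preference.

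**Working it through.** **Plan's own figure.** There is none to reproduce. The sample-size section covers success only and gives no SD, distribution or power for the VAS.

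**Inputs from the article.** One rating against a mean of two; two-sided independent-samples test; α = 0.05; 300 children, hence 300 / 2 = 150 per arm if allocation is equal.

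**Inputs assumed.** The VAS shape and the latent within-child correlation ρ between the two ratings (Gaussian copula). Every session has the same marginal distribution in both arms, so there is no true difference.

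**Step 1: closed-form illustration.** Let each rating be exponential with mean 20 and ρ = 0. Let X be one rating and Y the mean of two, which is gamma with shape 2 and scale 10.
- Means: E[X] = 20 and E[Y] = 2 × 10 = 20, so they are equal.
- Medians: X has 20 × ln 2 ≈ 13.9; Y has about 16.8.
- P(Y > X) = 1 − E[exp(−Y/20)] = 1 − (1 / (1 + 10/20))² = 1 − (2/3)² = 5/9 ≈ 0.556.

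The means agree, but the quantity that Mann-Whitney tests is not one half.

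**Step 2: why a floor does the same.** If half of ratings are zero and ρ = 0, a single rating is zero with probability 0.5, but a mean of two is zero with probability only 0.5 × 0.5 = 0.25.

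**Step 3: simulated rejection at nominal 5%, 150 per arm, no true difference.**

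| Assumed VAS shape | ρ = 0.2 | ρ = 0.4 | ρ = 0.6 | ρ = 0.8 |
|---|---|---|---|---|
| Symmetric (uniform) | about 5% | about 5% | about 5% | about 5% |
| Beta(1,4) | 16–18% | 12% | 8–9% | 6–7% |
| Beta(0.5,2) | 33–34% | 23–24% | 13–14% | 7–8% |
| 40% at floor, rest uniform | 24–28% | 19–21% | 14–15% | about 9% |

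Ranges cover repeated runs. Heavier floors are worse: with half of ratings at zero and the rest uniform, rejection is 26% at ρ = 0.5 and 13% at ρ = 0.8; with 70% at zero it is 41% and 20%.

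**Step 4: controls.** One rating against one rating returns Mann-Whitney to about 4% to 6%. A t test on one rating against a mean of two stays at about 4% to 6.5%, because the two expectations are equal. The excess therefore comes from pairing a single score with a mean of two under a rank test.

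**Step 5: sample size.** More children do not help. In the exponential case with ρ = 0, rejection is 20% at 66, 30% at 114 and 39% at 150 per arm.

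**Step 6: direction.** With right skew, nearly all excess rejections show the stepwise arm with the higher scores. Reversing the skew reverses the direction.

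**The case against.** The strongest reply is that the fault is conditional. The article names two tests and leaves the choice open, as an article may, and the t test option is sound. Mann-Whitney has to be chosen, the ratings have to be skewed, and a child's two ratings must not be highly correlated. The same child rates the same tooth after a similar procedure, so high correlation cannot be excluded. At ρ = 0.9 the rates for Beta(0.5,2) and Beta(1,4) are 5.9% and 5.0%. The number analysed would also fall below 150 per arm, because "Allocation will be performed via sealed opaque envelopes after the six-monthly recall examination" and drop-out is assumed at 20% a year. All of this stands and limits the size. It does not remove the fault, because the article itself both defines the unequal scores and permits the test that mishandles them.

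A second reply is that the root lies in the score definition. The first-session rating precedes allocation in both arms, so it cannot carry an effect of the strategy, and averaging it in dilutes any second-session effect. That is correct, but it is a separate matter: dilution hides a real difference, whereas the fault here creates a false one.

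Three stronger readings are tempting and are not supported:

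- That the analysis will declare a false preference. The article gives neither VAS shape nor correlation, so only a raised chance under stated assumptions can be shown.
- That a mean of two ratings can never be distributed like a single one. If a child gives the same rating twice, the mean equals that rating and the problem disappears.
- That the test is biased against stepwise excavation. The direction depends on where ratings pile up, and the article does not say.

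**Conclusion.** The plan is wrong as written on this point, in a limited sense: it permits a rank test on scores built from different numbers of ratings, and that test can reject when sessions are rated alike.

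The conclusion rests on two things. The first is the inference that selective children have a single rating. The second is the assumption that ratings are skewed or piled at one end with imperfect within-child correlation. Under those assumptions the error rate at 150 per arm is about 9% to 34% across the two beta shapes for correlations of 0.2 to 0.6, and about 14% to 28% with a 40% floor. At correlation 0.8 it is about 5% to 15% for most shapes tried, and higher only with floors of 60% or more (17% to 20%). With symmetric ratings or the t test there is no material inflation.

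The child VAS is a secondary outcome; the primary comparison of success is untouched.

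**What to change.** In Data analysis and statistical evaluation, state that Mann-Whitney will not be used where the stepwise VAS score is a mean of two ratings. Mean VAS will instead be compared with Welch's unequal-variance t test, or a bootstrap of the mean difference, and reported with a 95% confidence interval. Keep Mann-Whitney only where each child contributes one rating of the same kind in both arms. The first-session rating meets that condition, but it precedes allocation and so serves only as a baseline comparison. The choice of test for costs is not affected by this point.

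The change is one sentence and needs no new data. Its price is somewhat lower power than a rank test against some skewed alternatives.

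It corrects the error rate only. If the second-session mean is μ2 and the first-session mean is μ1, the stepwise score has mean (μ1 + μ2)/2 and the selective score μ1. The compared difference is then (μ2 − μ1)/2, half the change between sessions. That dilution remains until the score definition in Outcomes is revisited.

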## Methods/Design

### Overview

The planned study is a secondary care-based prospective, multicenter, two-arm parallel-group, randomized controlled trial at three pediatric university dental clinics in Germany: the Charité - Universitätsmedizin Berlin, the Ernst-Moritz-Arndt University Greifswald and the RWTH University of Aachen. We plan to enroll 300 patients with one or more deeply carious, sensitive and non-symptomatic deciduous molar. One molar per patient will be randomly allocated to receive one of two treatments (selective or stepwise excavation). The total follow-up time will be three years after completion of the initial treatment. Success, survival and restoration integrity will be assessed after one, two and three years. Patients’, parents’ and dentists’ preference will be assessed after each treatment using visual analogue or Likert rating scales. Costs will be assessed for the initial and follow-up treatments and will be based on a micro-costing approach. The study has been approved by the ethics committee of the Charité - Universitätsmedizin Berlin (approval number: EA4/057/14), the Ernst-Moritz-Arndt University Greifswald (approval number: BB 112/14) and the RWTH University of Aachen (approval number: EK 283/14). The study is registered at Clinicaltrials.gov (identifier: NCT02232828).

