**Table 3 Tab3:** **Handling of loss to follow-up**

**Level**	**Reason**	**Consequence**
Tooth	Complication	Complications leading to tooth loss will be counted as non-survival. Teeth with complications which allow the retention of the tooth will be count as non-success. Required follow-up treatments will be recorded and survived teeth will be followed up on.
	Lesion treated by other dentist	Tooth will be counted as non-success or non-survival.
	Tooth exfoliation	The last observation will be carried forward.
Patient	Adverse or serious adverse events related to treatment or material	Counteractive measures will be taken and events documented.
		Patient and tooth will be censored and the last observation carried forward.
	The patient cannot be examined (lost to follow-up)	Patient and survived tooth or teeth will be censored and the last observation carried forward.
	The patient decides to withdraw from the study.	Patient and tooth will be censored and the last observation carried forward.
Study	One to four patient(s) show adverse events related to treatment or material	Counteractive measures will be taken and events documented.
		Patient and tooth will be censored and the last observation carried forward. The study will be interrupted.
	More than four patients show adverse events or one patient shows a severe adverse event related to treatment or material	Counteractive measures will be taken and events documented.
		The study will be terminated. All patients and available teeth will be marked as censored and the last observation carried forward.

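### Follow-up costs are compared by tests that cannot use censoring, and carrying the last observation forward for lost children would understate retreatment cost

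*Protocol article*

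**What the plan says.** All places are in the protocol article.

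- **Hypothesis** (Objectives and hypotheses): "both initial and long-term costs of excavation methods are supposed to significantly differ".
- **Cost outcome** (Outcomes): "initial and follow-up treatment costs" are a secondary outcome, built from staff time, personnel and transport.
- **Collection** (Intervention and data collection; Table 2): costs are recorded at the first step, at the six-month step and at any retreatment. "If retreatments are required, the cost of these will be assessed as well".
- **Follow-up** (Overview): "The total follow-up time will be three years after completion of the initial treatment".
- **Test** (Data analysis and statistical evaluation): "two-sided independent t tests or Mann-Whitney U test (to compare visual analogue scale results and costs"). Log-rank tests are reserved for success and survival.
- **Loss to follow-up** (Table 3): "Patient and survived tooth or teeth will be censored and the last observation carried forward". Withdrawn patients get the same treatment. Costs are not mentioned by name.
- **Missing data**: drop-outs are to count as failures of success or survival, to allow for imbalanced loss. This assigns no cost.
- **Planned loss** (Sample size): "Assuming an annual drop-out rate of 20" per cent.

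**The concern.** A retreatment cost is seen only while the child is still attending. If a running cost total is carried forward from the last contact, the child is treated as having cost nothing more until month 36. A t test or Mann-Whitney test then takes that truncated figure as a finished observation, because neither test has a way to use a censoring indicator.

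Treatment cost up to the six-month step is largely observed, while later cost is not. The part that goes missing is therefore the part behind the long-term cost hypothesis. The Background names long-term cost as an evidence gap, and the Discussion wants cost-effectiveness to inform implementation. The Mann-Whitney option also does not compare mean costs.

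**Working it through.** **Inputs from the document.** Yearly drop-out is 20%, with one rate for both arms. Follow-up is three years, with allocation and the second step at six months.

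**Inputs assumed.** Loss occurs at a constant rate, retreatment cost accrues evenly, and loss is unrelated to cost. The document gives no unit costs, so the cost figures below are illustrations only.

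**1. The plan's own drop-out figure.** 66 × 1.2³ = 114.05, which reproduces the stated 114 per group. The plan therefore applies its 20% three times, once per year. (Dividing by 0.8³ would give 128.9; that is a separate matter and is not used here.)

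**2. Share of children with truncated follow-up.** 0.8³ = 0.512, so 51.2% complete three years and 48.8% do not.

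**3. Share of follow-up time observed,** f = (1 − (1 − d)^T) / (T × −ln(1 − d)):

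| Yearly loss d | Period | Observed | Unobserved |
|---|---|---|---|
| 20% | 3 years | 0.488 / (3 × 0.2231) = 72.9% | 27% |
| 20% | 2.5 years after allocation | 0.4276 / (2.5 × 0.2231) = 76.6% | 23% |
| 20%, all losses at year end | 3 years | (1 + 0.8 + 0.64)/3 = 81.3% | 19% |
| 20%, all losses at year start, or costs known only to the last annual visit | 3 years | (0.8 + 0.64 + 0.512)/3 = 65.1% | 35% |
| 10% | 3 years | 85.7% | 14% |
| 5% | 3 years | 92.7% | 7% |

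**4. Effect on the contrast when loss is equal.** Let D_E be the early-treatment difference and D_R the true retreatment difference, both stepwise minus selective. The truth is D_E + D_R. The carried-forward comparison estimates D_E + f × D_R, which lies between the truth and D_E.

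- D_E = +100, D_R = −30: truth 70, observed 100 − 0.729 × 30 = 78.1.
- D_E = +100, D_R = −100: truth 0, observed 100 − 72.9 = 27.1.
- D_E = +100, D_R = +100: truth 200, observed 172.9.

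If follow-up cost is tested on its own, the estimate is f × D_R. A true −30 becomes −21.9, which is a shrinkage towards zero.

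**5. Allowing for the six-month step.** The extra stepwise cost arises at month six. By then 1 − 0.8^0.5 = 10.6% have been lost. Take D_E = +100 and D_R = −100, with D_R accruing over months 6–36. Among children who reach allocation the observed difference is 100 − 76.6 = +23.4. If all included children are counted it is 89.4 − 0.894 × 76.6 = 89.4 − 68.5 = +20.9. The truth is 0 in both cases.

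**6. Unequal loss.** Take 10% yearly loss in the selective arm and 30% in the stepwise arm (f = 0.857 and 0.614), retreatment cost of 130 and 100, and D_E = +100. The truth is 70. The observed difference is 100 + 0.614 × 100 − 0.857 × 130 = 49.9, which is further from D_E than the truth is. With the two loss rates swapped it is 105.9.

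**The case against.** **The tested variable and the rule are partly inferred.** No sentence says that a three-year cost total is tested, and Table 3 is worded for patients and teeth, not costs. An article may leave the handling of incomplete costs to a fuller document. The first part stands, so the direction has to be given for both readings, total cost and separate follow-up cost. The second part does not remove the point. The article does name the tests and does give a general rule for lost and withdrawn children, and those two together understate retreatment cost on either reading.

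**20% is a planning allowance.** The earlier trials in Table 1 report yearly drop-out of 0–12%, and the eligibility criteria exclude families who plan to move. This stands, so the size is best read as a range. At 12% the same formula gives about 17% unobserved.

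**Even accrual is an assumption.** Only teeth expected to exfoliate within 18 months are excluded, so some teeth will exfoliate before month 36 and generate no later cost. That would make the unobserved share smaller. Carrying a cost forward after exfoliation is correct and is no part of the bias.

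**Stronger readings that a reader might infer.**

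- *The plan would get the sign of the cost difference wrong.* This is not supported. Moving from 0 to +27 is no reversal. With equal loss, a reversal needs a retreatment saving between 1 and 1/0.729 = 1.37 times the early extra cost, and no unit costs are given. If the assumed hazard ratio of 1.3 means more failures after stepwise excavation, both components have the same sign and none can occur under equal loss.
- *The contrast always moves towards the early difference.* This needs similar loss in both arms, and the Missing data section itself anticipates imbalance.
- *Early costs are seen in everyone.* Children lost before month six never reach the second step.

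**Conclusion.** The point holds with limits. Following the stated tests and the stated rule for lost children, mean retreatment cost is understated whenever children are lost before retreatments that would have cost something, because the unseen costs cannot be negative. The shortfall is about 23–27% at 20% yearly loss, given constant loss and even accrual.

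The direction of the bias in the comparison is conditional. With similar loss it is towards the early-treatment difference for a total cost and towards zero for a separate follow-up cost. With unequal loss it can be either. How far the estimated difference moves, and whether its sign could change, cannot be settled from the document. The point concerns a secondary outcome, but one with its own hypothesis, and it is worth correcting before analysis.

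**What to change.** - Do not carry costs forward for lost or withdrawn children. State that Table 3's carry-forward rule does not apply to costs.
- Estimate mean 36-month cost per arm by a censoring-adjusted method, for example inverse-probability-of-censoring weighting partitioned by follow-up period. Report the mean difference with a bootstrap 95% confidence interval.
- Count a tooth that has exfoliated or been extracted as having complete cost follow-up. Treating it as censored would overstate cost.
- Report treatment cost through the six-month step separately from later retreatment cost, and note that children lost before six months lack the second-step cost.
- Give the complete-case result as a sensitivity analysis, and show drop-out by arm so that the reader can judge the direction of any remaining bias.

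The cost is revised analysis wording and a little programming, with no new visits or data. The interval will be somewhat wider than the naive one. The weighting still assumes that loss is explained by what has been recorded.
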